## Abstract

**Introduction:**

Sexual and gender-based violence can have long-term impacts on the physical and mental health of survivors, with demonstrated impairments to immune, endocrine and nervous systems, and increased risk of chronic conditions such as cardiovascular disease, depression and post-traumatic stress. Moreover, survivors commonly experience low self-efficacy and lack of perceived control over their lives. Creating space for survivors to feel empowered through a multidimensional approach to health promotion, considering both physical and psychological influences on health, is necessary to reduce chronic disease.

**Methods and analysis:**

In this type II hybrid effectiveness-implementation cluster randomised controlled trial, we evaluate a novel peer-led intervention that combines expressive writing and trauma-informed boxing, Left Write Hook, against trauma-informed boxing alone—an intervention approach that is currently accessible in the community and has been shown to improve both mental and physical health. 20 clusters of 8–10 adults (n=150) with a self-reported history of child sexual abuse or other gender-based violence will be recruited in Melbourne, Australia, through health services and the community. Clusters will be randomly assigned to complete either 8× weekly group sessions of Left Write Hook (intervention) involving both expressive writing and trauma-informed boxing led by a trained peer facilitator, or 8× weekly group boxing sessions led by a trauma-informed boxing facilitator (control). Implementation will be evaluated against the PRISM Reach Effectiveness Adoption Implementation Maintenance (RE-AIM) framework. The primary effectiveness outcome is change in self-efficacy from preintervention to postintervention (8 weeks). Secondary effectiveness outcomes are changes in symptoms of complex post-traumatic stress disorder, trauma-related cognition and indicators of physical fitness (strength, flexibility, aerobic fitness and balance). Assessment will be completed online or over the phone with a member of the research team at preintervention (0 weeks), postintervention (8 weeks) and at 1 month following completion of the intervention (12 weeks). The primary implementation outcome is the fidelity of the train-the-champion implementation strategy for intervention training and delivery, and the secondary implementation outcome is adoption of the intervention and training delivery.

**Ethics and dissemination:**

Ethical approval was received from the Human Research Ethics Committee of The University of Melbourne (2024-28998-60131-11) and the Alfred Hospital Ethics Committee (110810). Results will be disseminated via publication in a peer-reviewed journal, and data will be made available via Open Science Framework at the conclusion of the trial.

**Trial registration number:**

ACTRN12624000862549.

STRENGTHS AND LIMITATIONS OF THIS STUDYSurvivor-designed and survivor-led peer intervention; consumer contributions shape the study design (outcomes, measures).The hybrid effectiveness-implementation design allows for insights to inform broader scale-up of peer-led interventions.The study employs a range of multidimensional outcome measures, including self-report mental health measures, physical and biological measures and semistructured qualitative interviews.This study is limited by the inability to mask those completing the in-person physical health assessments.Recruitment is restricted to a small number of sites, limiting implementation implications.

## Background

 Child sexual abuse and other forms of gender-based violence constitute a major public health concern with well-documented short- and long-term effects on the physical and mental health of survivors.^1 2^ Gender-based violence includes intimate partner violence, sexual violence and other harmful acts directed at individuals on the basis of their gender.^3^ It disproportionately impacts women, with 35% of women experiencing sexual or domestic violence in their lifetimes,^3^ as well as gender-diverse individuals, who face equivalent or even greater risk.^4^ Gender-based violence, particularly during childhood, increases the likelihood of chronic mental (eg, depressive and post-traumatic stress) and physical (eg, cardiovascular and respiratory) health disorders.^5 6^ The link between gender-based violence and chronic health conditions in adulthood represents a complex interplay of physical and psychological factors. Survivors have higher levels of stress, which can increase engagement in health risk behaviours such as reduced physical activity, substance use and unhealthy diet,^7^ each of which uniquely contributes to the development of chronic disease.^8 9^ This is in addition to the demonstrated negative impact of abuse (notably sexual abuse) on functioning of the immune, endocrine and nervous systems.^10^,^12^ These issues are compounded by systemic biases wherein the impact of trauma on physical health often goes unrecognised.^13^ A multidimensional approach towards health promotion, which dually considers physical and psychological health, is sorely needed to reduce chronic disease in this population.^14^

### Existing interventions

There are a number of gold-standard treatments that have established benefits for survivors, such as trauma-focused cognitive behavioural therapy and eye movement desensitization and reprocessing (EMDR).^15^ However, there are considerable barriers to accessing such treatments, notably due to the limited number of professionals trained to deliver them.^16 17^ Even if these barriers are overcome, these interventions predominantly emphasise alleviation of psychological symptoms.^15^ However, survivors also experience alterations in physiological stress responses, such as heightened threat detection and modified stress hormone patterns.^18^ Some evidence suggests that cognitive-based therapies do not adequately address these somatic impacts of trauma, with symptoms such as dissociation, insomnia and pain difficult to shift.^19^,^21^ Consequently, survivors often report feeling underserved by traditional approaches to mental healthcare that fail to address individual needs and the lasting impacts of trauma, leading to substantial treatment dropout.^22^
^23^ This highlights the need for alternative treatment approaches that overcome the limitations of existing clinician-delivered, cognitive-based therapies.

Here, we take a coproduction approach to evaluating a peer-delivered intervention for survivors of gender-based violence.^24^ In doing so, we seek to centre lived experience voices in setting research priorities and methodological design, ensuring that the peer-led nature of the intervention is also reflected in the research evaluating the intervention. By working closely with the survivor-led charity which designed and delivers our evaluated intervention, we provide a direct pathway for implementing our research outcomes for survivors of gender-based violence.

### Trauma-informed, peer-led interventions

Trauma-informed, peer-led interventions that centre survivors’ expertise in their own healing show potential to overcome the limitations of existing clinician-delivered therapies.^25^ Trauma-informed care encompasses principles of safety; trustworthiness and transparency; peer support; collaboration and mutuality; empowerment, voice and choice and cultural, historical and gender issues.^26^ Peer-led support programmes fit within this framework to create environments that privilege mutual support and relational healing while reducing power imbalances inherent in traditional therapeutic relationships.^25 27^ These survivor-centred approaches, facilitated by individuals with lived experience rather than mental health professionals, offer a promising alternative that can enhance treatment acceptability and help to overcome traditional barriers to care.^25^ Rather than positioning trained clinicians as agents of empowerment, peer support recognises survivors as central agents of their own recovery.^28^ Although growing evidence supports peer-led approaches for survivors, implementation challenges have hindered their adoption.^29^ Thus, scaling peer-led interventions requires systematic evaluation of both effectiveness and implementation outcomes. Essential implementation components include developing comprehensive training protocols and establishing accessible supervision structures that enable peer facilitators to deliver interventions safely (for both themselves and those they support) and effectively.^30 31^

### Writing-based interventions

There is a strong evidence base for the efficacy of writing-based interventions such as written exposure therapy,^32^,^34^ wherein survivors write expressively about the trauma with the guidance of a trained support person.^32^ As written-based therapeutic interventions require less specialist training and clinical expertise to deliver relative to current first-line treatments (eg, EMDR),^15^ they are well suited to peer delivery. Aligned with current first-line treatments, writing-based therapies facilitate the cognitive processing of trauma-related schema^35 36^ while developing capacity to tolerate and process difficult internal experiences.^34^ Writing about trauma in a supportive peer environment may strengthen survivors’ coping skills by teaching them that their trauma memories are not dangerous, that distress associated with recalling trauma is both tolerable and transient and that it is possible to develop new perspectives on trauma and its meaning.^32^ In addition to established effects for psychopathology, including reductions in symptoms of post-traumatic stress disorder (PTSD), anxiety and depression,^37^,^39^ there are some suggestions that expressive writing is associated with improvements for both objectively assessed and self-reported physical health outcomes.^40^ While writing offers valuable benefits for trauma processing,^35 36^ an important therapeutic goal for survivors is to reconnect with and regain agency over their bodies.^41^ Moreover, recent evidence has demonstrated that augmenting trauma-focused exposure therapy with aerobic exercise can improve therapeutic outcomes.^42^ Accordingly, incorporating embodied practices that help survivors ground themselves in the present and reconnect with their physical self after engaging with trauma memories through writing may therefore enhance therapeutic effects.

### Body-based interventions

Integrating body-based and cognitive techniques may better address survivors’ diverse needs and promote sustained recovery outcomes.^43 44^ There are a number of body-based therapeutic techniques which are beneficial for trauma survivors.^44^ In particular, non-contact boxing offers promise as a modality to help survivors reconnect with their bodies and ground into the present. Non-contact boxing combines high-intensity training and bodily awareness through techniques including stretching, skipping, shadowboxing, pad work and bag work.^45^ It is shown to foster an enhanced sense of empowerment and ability to locate healthy aggression in survivors,^46^ along with increases in agency, resilience, self-esteem and perceived physical ability.^47^ Encouragingly, exercise-based adjuncts fit easily into peer-delivery models and have demonstrated impacts for survivors in improving symptoms of PTSD, depression and anxiety.^45^ Improvements extend beyond mental health, with evidence of physical activity interventions reducing risk of chronic disease (including cardiovascular, respiratory and type 2 diabetes) by up to 80%.^48^ Given potential benefits for improving both mental and physical health in survivors, combining this physiological-based approach with an established psychological technique such as expressive writing may help to enhance outcomes for survivors.

In sum, current research suggests that a programme that incorporates both a physical health component and a psychological component may increase treatment benefits for trauma-exposed individuals.^42 49^ However, the unique combination of expressive writing and non-contact boxing is yet to be evaluated. These components can be delivered in a group-based setting, conferring additional benefits such as decreasing stigma and shame and enhancing social connection.^50^ Critically, this combined approach is suited to peer delivery, and taking a peer-led approach may further increase the acceptability and accessibility of support programmes.^51^

### Left Write Hook

Here, we seek to trial a novel intervention, Left Write Hook, which combines expressive writing and non-contact boxing within a peer-delivery model. Left Write Hook is a survivor-designed intervention, developed independently by a survivor of child sexual abuse in the community (ie, rather than formally developed within a research context). The programme was borne from the founder’s own lived experience of gender-based violence and reflection on an unmet need for connection with others who shared similar experiences to her own. In considering how to foster a space in which survivors could come together as part of a shared journey towards healing, she recognised the profound impact of both creative practices (eg, expressive writing, as opposed to written exposure techniques) and movement-based practices (eg, boxing) in her own healing journey and noted that such practices were often lacking from commonly offered psychological therapies (eg, cognitive behavioural therapy, cognitive processing therapy and EMDR). Initial efforts included establishing a support group that came together to practise writing and boxing in a peer-led manner and which received significant support within her local community. Subsequently, the Left Write Hook founder sought to formalise the programme through the development of a manualised programme, ultimately establishing a charity which is funded by philanthropic contributions to deliver the programme across Victoria. Concurrently, the Left Write Hook charity sought to partner with researchers to formally establish the feasibility and acceptability of the intervention.^52^

Left Write Hook is a survivor-led programme delivered via 8× weekly 2-hour group-based sessions in a community setting. Each session has two components: expressive writing and trauma-informed non-contact boxing. Participants are invited to write to prompts designed to encourage meaning-making from past experiences, with the option of sharing with the group to foster expression and validation. Trauma-informed non-contact boxing combines the approach of trauma-informed care with the physical activity of boxing, inviting participants to connect with their bodies through grounding, stance and focus on purposeful movement in a way that caters to their individual needs. Left Write Hook has the potential to expand beyond the established benefits of non-contact boxing alone through three key enhancements: the peer facilitator model encourages social connection and belonging; the additional writing component enables individuals to reclaim their life narratives and process difficult internal experiences; and the empowerment focus carries themes from the writing through to the boxing components to encourage grounding into the self and expression through physical movement.

As noted earlier, prior research on the Left Write Hook has been conducted concurrently with the dissemination of the programme in the local community within which it was established. After the programme was developed, a pilot study was conducted with adult survivors of child sexual abuse to investigate the efficacy of the programme and potential for future expansion.^52^ Large effect sizes were seen for preintervention to-postintervention improvement on a self-report measure of emotional, social and psychological well-being (Cohen’s *d*=0.99), alongside clinically meaningful reductions in PTSD symptomatology (Cohen’s *d*=1.02).^52^ Survivors who completed the programme experienced a large increase (Cohen’s *d*=1.48) in the self-reported ability to assert oneself, affect one’s environment and perform actions.^52^ This increased self-efficacy was reflected in qualitative analysis which demonstrated that the expressive writing promoted themes of participant empowerment, validation and connection to one’s body (eg, ‘I want to fix my body and my mind and feel strong’), with writing outputs reflecting that these themes evolved positively across the course of participation. Demonstrating feasibility and acceptability, validation of participants’ stories and feelings also emerged as a key qualitative theme, and 80% of participants completed all sessions and research measures. A formal evaluation of programme efficacy, acceptability and feasibility is now needed.

### Self-efficacy

There are multiple processes of change which may drive improvements in both mental and physical health, and our pilot data suggested that Left Write Hook may exert its effects by empowering survivors. Here, we evaluated programme effects on self-efficacy for a number of reasons. First, the General Self-Efficacy Scale^53^ has strong psychometric properties and incorporates elements of agency, assertiveness and control to assess individuals’ belief in their overall capability to succeed—factors which all improved in our pilot data. Self-efficacy is persistently low in survivors, reflecting pervasive perceptions of a lack of self-agency and power over their own lives.^54^ Similarly, survivors may mentally disconnect from their bodies (ie, dissociate) in order to cope with their experiences and can, as a result, feel a lack of agency over their own bodies.^55^ Critically, self-efficacy is longitudinally associated with mental and physical health outcomes in both community and trauma-exposed populations, with greater self-efficacy linked to decreases in PTSD symptoms, self-report pain, fatigue and substance use, alongside increases in physical activity.^56^,^58^ Finally, aligned with our coproduction approach, survivors were central to deciding the primary outcome for this trial. Our lived experience advisors stressed the importance of an outcome measure that is recovery-oriented rather than symptom-based, which reflects how the survivor is moving forward with their life rather than emphasising ongoing challenges. We therefore considered intervention efficacy on self-efficacy, with secondary outcomes of mental and physical health.

### Implementation

Beyond establishing treatment efficacy, considering implementation is essential for new interventions. A significant gap often develops when translating treatments developed within controlled research settings into real-world mental health settings.^59^ Treatment fidelity, the degree to which interventions are delivered as intended, presents a fundamental challenge, as real-world delivery often deviates substantially from original protocols.^60^ These challenges may be particularly pronounced in peer-delivery models, where facilitators have diverse professional backgrounds and experience.^61^ Additionally, working with survivors of gender-based violence who often have complex and diverse needs may create tension between protocol adherence and dynamic, person-centred care. Maintaining intervention fidelity is essential not only to ensure treatments achieve their intended effects but also to inform effective scaling to new contexts.^60^ Therefore, systematically assessing fidelity across both training and delivery phases is fundamental to ensuring new interventions can be implemented safely and effectively in diverse settings.^62^ Our use of a hybrid effectiveness-implementation trial design allows dual consideration of a primary effectiveness (individual-level) and primary implementation (individual level and site-level) outcomes,^62^ enabling formal evaluation of both the potential benefits of the intervention for survivors and the acceptability and feasibility of intervention delivery within established organisations (health services and charities) which support survivors.

### The current study

We aim to complete a hybrid effectiveness-implementation cluster-randomised control trial to both evaluate the impact of Left Write Hook on the self-efficacy of adult survivors of child sexual abuse and gender-based violence and concurrently develop and evaluate the fidelity of a train-the-champion implementation strategy for delivery in new settings. Alongside assessing effectiveness, an implementation evaluation is essential to establish to inform intervention scalability as well as address apprehensions around peer support programmes for survivors.^27^ We hope that insights into the implementation of Left Write Hook will help to inform training and delivery models of peer-led interventions for survivors more generally.

We compare Left Write Hook to a control group of trauma-informed non-contact boxing only, delivered by a personal trainer (rather than a fellow survivor), akin to the type of current evidence-based programme survivors can access in the community. The resource (ie, both interventions able to be delivered by non-psychologists) and time commitment for participants were matched between trial arms. We hypothesise that those completing Left Write Hook will experience a greater improvement in self-efficacy, relative to the control intervention, at postintervention.

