### Intervention

#### Left Write Hook

Left Write Hook is delivered via 8× weekly 2-hour group-based sessions in a local gym/sports centre or community room. Sessions are led by two paid peer facilitators: a lead facilitator, assisted by an assistant facilitator, both of whom are survivors themselves. All peer facilitators are paid in line with industry rates for casually employed facilitators of exercise-based interventions. Each session has two components: expressive writing and trauma-informed non-contact boxing. An outline of the full programme, including session themes, is shown in table 1.

**Table 1 T1:** Outline of Left Write Hook programme

Week	Theme	Primary session goal
1	Grounding	Help people feel comfortable in the space and instil participants with a sense of purpose and feeling of being grounded.
2	Balance	Teach participants how to channel their emotions through the boxing. Create a safe environment for difficult emotions.
3	Expression (fluidity)	Help guide participants through difficult emotions and help them feel comfortable expressing themselves through writing and boxing. Give participants a healthy outlet.
4	Lightness	To have participants feeling lighter and more accomplished. To have participants feeling confident with their boxing.
5	Taking back your power	To have participants feeling confident in their boxing capabilities. To give participants the ability to harness their power.
6	Fighting Back	Give participants the building blocks to defend themselves. Have participants feel confident with weaving and pad work. Have the participants understand and express healthy aggression.
7	Rewriting narratives	To have participants take back their personal power
8	Imagining futures	To have participants be ready for the next steps in life once the programme ends, whether their next step is to return, become a facilitator or leave with a more positive outlook on life moving forward.

Writing prompts reflect the theme of each session.

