The first hour involves participants writing to recovery-focussed prompts designed to reclaim their life narrative and encourage meaning-making (eg, ‘fighting back means…’), with the option of sharing with the group to encourage expression and validation. Writing prompts reflect the theme of each session. Participants are invited to write about anything that comes to mind for them in response to the writing prompts and session theme. While this means that they are not required to write about past trauma and may choose to write about any topic, participants do predominately choose to write about their experiences of trauma or its impact on them. Peer facilitators guide the expressive writing and also participate in the writing and sharing. Next, participants complete a 45-min trauma-informed non-contact group boxing session. Peer facilitators guide participants to connect with their body and locate an empowered state, carrying through the theme from the expressive writing to guide participants’ focus on stance, punch, direction and movement. Each session ends with 15 min of grounding and reflections. Details on how the principles of trauma-informed care are embedded within the programme are outlined in table 2.

**Table 2 T2:** Examples of trauma-informed considerations across interventions and research procedures

Programme element	Trauma-informed principle(s)^25^
*Intake*	
Use inclusive and easy to understand language	Empowerment, voice and choice
Provide clear and detailed information on what the programmes involve	Safety, trustworthiness and transparency
Collaborative decision-making with potential participants regarding programme suitability at this time	Empowerment, voice and choice
Establish confidentiality and safety regulations	Safety, trustworthiness and transparency
Let survivors choose to share or withhold	Empowerment, voice and choice
*Both Left Write Hook and boxing-only interventions*	
Female or gender-diverse facilitators	Empowerment, voice and choice
All facilitators trained in trauma-informed facilitation	Safety, trustworthiness and transparency
Venue selection (accessibility, private space, limiting mirrors, quiet break-away space)	Safety
Invitational facilitation style to promote agency and choice	Safety, empowerment, voice and choice
Facilitators complete in-person research assessments, not trial staff	Safety, trustworthiness and transparency

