#### Active control: boxing-only

Participants randomised to control will complete 8× weekly group sessions of trauma-informed non-contact boxing, without writing and without a specific focus on empowerment, to control for the positive effects of exercise on self-efficacy. Each week, participants will complete a 45-min group boxing session, led by a boxing instructor (ie, intervention is not peer-led) at the same sites as the intervention arm. This replicates the type of trauma-informed exercise class that survivors could access in their local community. Boxing was selected as the exercise modality based on consumer input that identified it as the most acceptable exercise option for an active control, particularly in the context of consenting to randomisation. The control group therefore represents trauma-informed exercise options as usual, without three unique components of the Left Write Hook intervention: the peer-led nature of intervention, expressive writing and the focus on empowerment that links from the expressive writing to the trauma-informed non-contact boxing component to encourage expression through physical movement. Trauma-informed considerations for the boxing-only group are outlined in table 2.

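### Participant time is said to be matched between arms, but the stated session lengths give 16 hours of group contact against 6

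*Protocol article*

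**What the plan says.** In the protocol article, The current study (end of Background) introduces the comparator and states that the resource (which it defines as delivery by non-psychologists) and "time commitment for participants were matched between trial arms".

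The Methods then describe each arm.

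- **Intervention (Left Write Hook):** "Left Write Hook is delivered via 8× weekly 2-hour group-based sessions in a local gym/sports centre or community room". The same section breaks the session down. "The first hour involves participants writing to recovery-focussed prompts"; 45 minutes of boxing and 15 minutes of grounding and reflection follow.
- **Control (Active control: boxing-only):** eight weekly group sessions, where "Each week, participants will complete a 45-min group boxing session, led by a boxing instructor (ie, intervention is not peer-led". No other activity is described for these participants.

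The control section goes on to describe that arm as being "without three unique components of the Left Write Hook intervention": peer leadership, expressive writing, and the empowerment focus that carries over from the writing into the boxing. Contact time is not listed as a difference.

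**The concern.** The article states a property of the design and then describes a design that does not have it. A 2-hour and a 45-minute weekly session are different time commitments.

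The statement matters because of the kind of outcome being compared. The primary effectiveness outcome is the participant's own score on the General Self-Efficacy Scale. Randomisation and blinding explains the single masking through the independently generated allocation list and the masked biostatisticians, and describes no masking of participants. With a self-reported psychological outcome of this kind, more time in a supportive group is a natural rival explanation for a benefit.

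A reader who is told that time was matched, and that the control lacks three named components, would take that explanation as already ruled out by design. It is not. If the sentence passes into the results paper, a positive finding would look more specific to peer leadership, writing and empowerment than the comparison allows.

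**Working it through.** **Inputs, all from the protocol article**

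| Quantity | Left Write Hook | Boxing-only |
|---|---|---|
| Weekly sessions | 8 | 8 |
| Writing per session | 60 min | none |
| Boxing per session | 45 min | 45 min |
| Grounding and reflection per session | 15 min | none described |

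**Step 1. Reproduce the stated session length.** 60 + 45 + 15 = 120 min, which is exactly the 2 hours given for Left Write Hook. The intervention description is internally consistent.

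**Step 2. Scheduled contact per participant.** Total = sessions × session length.

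- Left Write Hook: 8 × 120 min = 960 min = 16 h.
- Boxing-only: 8 × 45 min = 360 min = 6 h.

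**Step 3. Size of the gap.**

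- Difference: 16 − 6 = 10 h.
- Ratio: 16 / 6 = 2.67.

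**Step 4. Where the extra time lies.**

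- Writing: 8 × 60 min = 8 h.
- Grounding and reflection: 8 × 15 min = 2 h.
- Boxing: 8 × 45 min = 6 h in each arm, so no difference.
- Check: 8 + 2 = 10 h, which accounts for the whole gap.

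**Step 5. What is matched.** The number of weekly sessions (8) and the boxing time (6 h) are equal. Total participant time is not.

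**Step 6. Effect on the statistical plan.** The sample size rests on a difference of 3 points, an SD of 5.6, an intraclass correlation of 0.02, 80% power and a two-sided 5% level. None of these depends on contact time, so no figure there changes.

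**The case against.** The case for leaving the text alone has several parts.

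**Matched time could mean matched attendance.** Both arms attend once a week for eight weeks. The sentence does not say this, however; it speaks of time commitment without qualification. This reading shows what the authors may have intended, and does not make the wording correct.

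**The control does its stated job.** The control section says the arm is there to account for the benefit of exercise and to represent the trauma-informed exercise classes available in the community. Boxing time is equal, so that purpose is met. This stands. An attention-matched control would be a different design, and its absence is not an error.

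**Most of the extra time is a named component.** Eight of the 10 hours are the writing itself. The other 2 hours are arguably linked to the empowerment focus, which the Left Write Hook section of the Background connects with grounding. This also stands, and it limits the point. A reader might infer that a difference could not be credited to the three components at all. The documents do not support that. What follows is narrower: the effect of those components and the effect of the time they occupy cannot be told apart.

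**The planned question is about the programme.** The primary question under Statistical analysis plan compares the whole programme with boxing-only, and no component-level analysis is described. This is correct, and it is why the defect concerns description and interpretation and does not touch validity.

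Two stronger readings are tempting and should not be adopted.

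- A reader might infer that the resource claim is also false, because "Sessions are led by two paid peer facilitators" while the control has a boxing instructor. The sentence defines resource as delivery by non-psychologists, and both arms satisfy that. Nor does the article state how many staff run a control session. A single instructor is only a reading of the singular noun, and the fidelity section has a lead and an assistant completing checklists without limiting this to one arm. No comparison of staff hours can be built on this.
- A reader might infer that a cost comparison between arms will be distorted. The article says that training and delivery costs will be tracked and that the costs and benefits of Left Write Hook will be explored. It describes no between-arm cost comparison.

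**Conclusion.** The time-matching statement is contradicted by the article's own session lengths: 16 h against 6 h of scheduled group contact, 10 h more and 2.67 times as much. Contact time is also left out of the account of how the arms differ. Any effect of peer leadership, writing and empowerment is therefore inseparable from the effect of the added group time.

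This is a moderate defect of description and interpretation. It does not undermine the randomised comparison of the whole programme with boxing-only, and it changes no sample size, power figure, significance level or model.

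The figures rest on two assumptions: that the session lengths in the Methods are those actually delivered, and that control participants have no further scheduled group time that the article omits. They are scheduled hours; attended hours may differ.

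**What to change.** 1. Reconcile the sentence in The current study with the session descriptions under Left Write Hook and Active control: boxing-only. Which of them is right is for the trial team to establish.
2. If the session lengths stand, replace the time-matching claim with a statement that the number of weekly sessions and the boxing time were matched.
3. In the control section, add total group contact time (16 h against 6 h) to the listed differences between arms.
4. State, in the analysis plan and the results paper, that the trial estimates the effect of the whole programme against a 45-minute boxing class and does not control for contact time.
5. Report attended time by arm, for example sessions attended × session length. Non-attendance is already listed among the intercurrent events to be tracked; this report needs attendance recorded session by session.

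The cost is wording and one descriptive table. Delivery, sample size and the primary model stay as they are. The detailed analysis plan is still to be written before database lock and recruitment is expected to run until June 2026, so the correction can be made before results are available.
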